### Measurements

All participants will be asked to complete an online questionnaire at baseline, 6 months, and 12 months after baseline. GPs and PNs will not be present during the self-report questionnaire (participants will complete this assessment digitally at home). Therefore, no influence of the GP or PN on the Patient Reported Outcome Measures is expected. The questionnaires will measure self-reported lifestyle behaviors, behavioral determinants, and experienced psychological problems (see the *Outcomes* section).

The second questionnaire, administered 6 months after baseline, will also include items measuring health-related costs and, for intervention group participants only, a process evaluation questionnaire. In addition, biomedical measurements will be taken from all participants at 6 months after baseline. Blood pressure, total cholesterol/high-density lipoprotein cholesterol, and blood glucose were originally planned for the biomedical measurement. However, due to current circumstances in Dutch primary care (see the *Discussion* section), total cholesterol/high-density lipoprotein cholesterol and blood glucose measurements will be discontinued in consultation with the funding agency.

Nonresponse will be prevented by using previously effective protocols, including automated reminders 1 week and again 3 weeks after the distribution of questionnaires to patients [7,21] and email reminders to GPCs to ensure blood pressure measurement at 6 months. The quality control procedures ensure that there will be little nonresponse [8-11]. To improve the engagement of GPCs, relationships will be maintained through regular emails or phone calls to the designated contact person. In addition, a Christmas card will be sent each year on behalf of the research team. In addition, the GPCs will be offered support in patient selection and patient contact by a researcher on several occasions during this study.

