### Outcomes

#### Overview

The primary outcomes of this study are changes in lifestyle behaviors, measured by validated self-report questionnaires. PA will be assessed using the self-report Short Questionnaire to Assess Health [22,23]. Smoking behavior will be assessed using a validated (self-report) abstinence scale [24,25]. Alcohol consumption will be measured using a standardized alcohol consumption scale [26]. Dietary behavior will be assessed using a food frequency questionnaire on saturated fat intake and fruit and vegetable consumption [27-29].

Secondary outcomes are changes in experienced psychosocial problems such as anxiety and depression, fatigue, health-related QoL, and health-related costs, which will be assessed using validated self-report questionnaires. Anxiety and depression will be assessed using the Hospital Anxiety and Depression Scale [30,31]. Fatigue is assessed using the Checklist Individual Strength [32,33]. Health-related QoL is measured using the abbreviated European Organisation for Research and Treatment of Cancer Quality of Life Questionnaire [34,35]. Health-related costs are considered from a societal perspective and are measured as health care consumption in the last 3 months using the Institute for Medical Technology Assessment Medical Consumption Questionnaire, productivity losses in the last 4 weeks for both paid and unpaid labor using the Institute for Medical Technology Assessment Productivity Cost Questionnaire, and quality-adjusted life years (QALY) using the EQ-5D-5L [25,36-42]. All questionnaires used are validated, we do not conduct additional validation research as part of this research project.

Secondary outcomes are also blood pressure measurements, taken from all participants at 6 months postbaseline. Blood pressure will be assessed by clinical measurements performed by GPP.

In addition to outcome measures, relevant medical data (type of cancer, time since diagnosis, type of treatment, and recurrence) and social demographics (age, sex, level of education, income, living situation, comorbidities, and BMI), as well as intention toward PA, healthy diet, reduced alcohol consumption, and smoking cessation will be assessed at baseline. Items assessing recurrence, use of cointerventions, BMI, and lifestyle behavioral intentions will be repeated at the 6-month measurement and 12-month assessments.

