### Statistical Methods

#### Overview

The first 2 steps of the analysis will test for statistical differences at baseline in lifestyle behaviors, QoL, demographics, and psychosocial and medical symptoms between the 2 study groups. Blinding of the analyst will be applied for primary outcomes. Patterns and mechanisms of missing data will be explored. Thereby, special attention will be paid to dropouts. Randomization of the GPCs should account for an even distribution between the experimental and control conditions of socioeconomic factors or other confounding factors that may skew our results. However, in case conditions are unbalanced, these factors will be adjusted for in the analysis. If necessary, other statistical adjustment procedures will be applied to minimize the impact of any bias.

Multilevel linear regression analyses will be conducted to test for differences in residual change scores between the intervention and control groups on the primary and secondary outcomes at the 6-month follow-up and the 6- and 12-month follow-up combined. Intention-to-treat (ITT) analyses with multiple imputations will be applied. Participants will be nested within GPCs to account for potential interdependence between participants. Multilevel linear regression analyses with a random intercept for GPC level will be performed to account for possible interdependence in the effect analyses. The effects on the population will be assessed via CIs.

The primary outcome measures will be the residual change scores in lifestyle behaviors, but also differences in the secondary outcomes (anxiety and depression, fatigue, [health-related] QoL, and health-related costs). Blood pressure at 6 months will be compared between the intervention and control groups. In addition, moderation analyses will be conducted to examine different potential moderators such as age, gender, type of treatment, and level of education [8-11]. Subanalyses may be performed to explore individual differences that may be attributed to the degree of participation in the intervention. Besides factors on the level of participants, factors on the level of GPCs will be considered for further analysis. Finally, process evaluation data will be analyzed and summarized descriptively.

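### Blood pressure is read only at 6 months, so the residual-change rule cannot cover it; its 6-month comparison is valid but imprecise, with no check on starting balance

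*Protocol article*

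**What the plan says.** Three sections of the protocol article time blood pressure, and all give the same single time point.

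- Outcomes, Overview: "Secondary outcomes are also blood pressure measurements, taken from all participants at 6 months postbaseline". The same section adds: "Blood pressure will be assessed by clinical measurements performed by GPP" (GPP are the general practice personnel).
- Measurements: "In addition, biomedical measurements will be taken from all participants at 6 months after baseline". Two of the three biomedical measures were then dropped: "total cholesterol/high-density lipoprotein cholesterol and blood glucose measurements will be discontinued in consultation with the funding agency". Blood pressure is the only clinically measured outcome left.
- Statistical Methods, Overview: "Blood pressure at 6 months will be compared between the intervention and control groups".

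The baseline assessment is a questionnaire: "All participants will be asked to complete an online questionnaire at baseline, 6 months, and 12 months after baseline". The list of baseline data in Outcomes includes age, sex, BMI and comorbidities, but not blood pressure.

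Statistical Methods also has a general rule. Multilevel regression will "test for differences in residual change scores between the intervention and control groups on the primary and secondary outcomes at the 6-month follow-up", and again at 6 and 12 months combined. Baseline differences are to be tested, and unbalanced factors adjusted for. A random intercept for GPC is planned. Allocation is simple 1:1 by GPC (Randomization), with no stratification or balancing stated.

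**The concern.** A residual change score needs a baseline value, and a combined 6- and 12-month analysis needs a 12-month value. Blood pressure has neither. As a secondary outcome it falls under the general rule as worded, yet that rule cannot be carried out for it, and the later sentence gives it a different analysis. An analyst following the text has two instructions that disagree.

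The design consequence is separate. Without a starting value, blood pressure loses the precision that baseline adjustment gives the other outcomes. The plan's test-then-adjust step cannot cover starting blood pressure, and multiple imputation of missing 6-month readings lacks an obvious predictor. This matters more here than in a large trial, because allocation is unrestricted and 26 GPCs were recruited against a target of 40 (Strengths and Limitations). What is at stake is how much the one remaining clinical measurement can tell the reader.

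**Working it through.** **Inputs from the protocol article.** Intracluster correlation (ICC) 0.03, design effect 1.27, about 40 GPCs of 10, 282 participants required, 25% dropout (Sample Size); 127 participants in 26 GPCs (Results).

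**Assumptions not in the document.** Systolic SD 18 mmHg; the plan's ICC of 0.03 also holds for blood pressure; equal arms; correlation r between a starting and a 6-month reading of 0.4 to 0.7; normal multiplier 1.96, with no small-sample correction.

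1. *The plan's own figure.* Design effect = 1 + (10 − 1) × 0.03 = 1.27, which reproduces. The plan gives no precision figure for blood pressure.

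2. *Precision at the recruitment reported.* Mean cluster size 127/26 = 4.88, so the design effect is 1 + 3.88 × 0.03 = 1.12. SE of the arm difference = 18 × √(4 × 1.12/127) = 3.38 mmHg, or 0.188 SD. The 95% half-width is 1.96 × 3.38 = 6.6 mmHg, or 0.37 SD.

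3. *Range.*
   - ICC 0.01 to 0.10: ±0.36 to ±0.41 SD, about 6.4 to 7.4 mmHg at SD 18.
   - SD 16 or 20 mmHg: 0.368 × 16 = 5.9 and 0.368 × 20 = 7.4 mmHg.
   - 25% dropout (95 analysed, design effect 1.08): SE 3.84, half-width 7.5 mmHg.
   - 282 participants in 40 GPCs: SE 0.129 SD, half-width 0.254 × 18 = 4.6 mmHg.

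4. *Chance starting difference.* The SE in step 2 also describes the difference between arms at the start. The chance of exceeding 3 mmHg is 2 × (1 − Φ(3/3.38)) = 37%; of exceeding 5 mmHg, 14%.

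5. *How much reaches the result.* The expected carry-over is r × the starting difference. For r = 0.4 to 0.7, a 3 mmHg difference moves the 6-month comparison by 1.2 to 2.1 mmHg, and a 5 mmHg difference by 2.0 to 3.5 mmHg.

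6. *Validity.* In 10,000 simulated trials with no effect (26 GPCs of 5, ICC 0.03, r = 0.6), the 6-month-only comparison had mean error 0.00 and type I error 5.0% when clustering was respected. The slope of the result on the starting difference was 0.60, equal to r.

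7. *What a starting value could buy.* Adjusted half-width = 6.6 × √(1 − r²); equivalent extra participants = 1/(1 − r²) − 1.

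| r | Half-width (mmHg) | Equivalent extra participants |
|---|---|---|
| 0.4 | 6.1 | 19% |
| 0.5 | 5.7 | 33% |
| 0.6 | 5.3 | 56% |
| 0.7 | 4.7 | 96% |

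**The case against.** The best defence is that the plan does not really intend a residual change score for blood pressure. Outcomes describes the other secondary outcomes as changes and lists blood pressure apart from them. Statistical Methods names the other secondary outcomes in brackets without blood pressure, then gives it a separate analysis that can be carried out. This stands: only the general phrase brings blood pressure under the rule. A reader might infer that the planned analysis is impossible, and the documents do not support that. What remains is a conflict of wording.

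A reader might also infer that a chance starting difference goes unreduced into the result, or that the result cannot be told apart from a pre-existing difference. Neither follows. Only the fraction r carries over, the expectation under randomization is zero, and the standard error from the GPC random-intercept model already contains this variability. The 37% and 14% in step 4 describe the starting difference; setting them beside the half-width as an added harm would count the same variation twice. Nor do they make a large imbalance likely.

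Two limits on importance also stand. Blood pressure is one secondary outcome, and the sample size rests on lifestyle behaviors. It is also measured by practice personnel in unblinded GPCs, so it is not an assessor-blinded endpoint, and a baseline reading would not change that.

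The adjustment rule is not empty for this outcome, since demographic and medical factors collected at baseline could enter. It cannot reach starting blood pressure itself, and it acts only if imbalance is seen. Finally, the article condenses a fuller protocol, but it states the 6-month timing outright in three sections, so the timing is not a detail lost in shortening.

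**Conclusion.** The point holds as a wording conflict and a precision weakness, not as bias. The residual-change and combined 6- and 12-month analyses cannot apply to blood pressure, and the general sentence must be reconciled with the one comparing 6-month values. That comparison is sound under randomization with a GPC random intercept.

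Its 95% half-width is about ±6.6 mmHg at the recruitment reported, or 7.5 mmHg after 25% dropout, and balance in starting blood pressure cannot be examined. In SD units the half-width of 0.37 exceeds the effect size of 0.30 that the plan uses for its sample size, so an inconclusive blood pressure result would say little. The mmHg figures rest on the assumed SD, equal arms and the plan's ICC; the possible gain from an earlier reading rests on an assumed r.

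**What to change.** 1. In Statistical Methods, limit the residual-change analysis and the combined 6- and 12-month analysis to outcomes with a baseline value. State that blood pressure is a 6-month-only comparison in the multilevel model with a GPC random intercept. Cost: wording only.

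2. Prespecify age, sex, BMI and comorbidities as fixed covariates in that model, whether or not the arms look unbalanced. All four are already collected at baseline, so this needs no new data and replaces a data-driven choice.

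3. Optionally, where the GP record holds a dated reading from before the participant's baseline, add it as a covariate in a supplementary analysis and report how many participants have one and how old the readings are. The documents do not establish that such readings exist. They may be old, missing, or present selectively, because usual care is described as mostly complaint-driven (Intervention Procedure); this also makes imputing them doubtful. Extraction adds work for GPCs already short of capacity and may need a small ethics amendment. The gain, a half-width of about 6.1 to 4.7 mmHg, depends on r = 0.4 to 0.7.

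Items 1 and 2 should be settled before blood pressure is examined by arm; analysis was expected to start in spring 2025 (Results). The report should describe blood pressure as a lower-precision comparison without a baseline check.

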#### Sample Size

The effect evaluation of the online CAG intervention showed small to medium effect sizes (ES=0.20-0.40) on lifestyle behaviors at 6 months. In the current design, we expect an ES of 0.40 at 6 months follow-up [8]. Based on previous research on computer-tailored lifestyle interventions, we estimate an ES of 0.30 at 12 months [8,43-48]. Based on CAG data and other research in the primary care setting [49], we estimate an intracluster correlation of 0.03 to account for the multilevel design. Sample size calculation (ES=0.30; power=0.80; intracluster correlation=0.03, design effect 1.27) indicates that 282 participants are required for the effect study (141 in each condition). From 2 previous RCTs of online lifestyle interventions in patients or survivors of cancer, we know that dropout is 20%-25% [8,48]. Accounting for a 25% dropout, 376 survivors of cancer need to start in the RCT (188 per condition).

Furthermore, based on cancer prevalence figures, cancer survival rates, and the number of GPCs in the Netherlands, we expect that a standard GPC (consisting of 1-4 GPs and additional PNs) will have at least 20-40 survivors of cancer who meet the inclusion criteria. Therefore, to achieve a sufficient sample size, we aim to recruit approximately 40 GPCs, each of which will recruit 10 participants.

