#### Economic Evaluation

To calculate QALYs, utility scores will be obtained from the EQ-5D-5L scores and multiplied by the duration of follow-up (12 months). The economic evaluation will be conducted from a societal perspective and will therefore include medical costs (as measured by the Institute for Medical Technology Assessment Medical Consumption Questionnaire at T1), productivity costs (as measured by the Institute for Medical Technology Assessment Productivity Cost Questionnaire at T1), and costs of the blended care intervention. Intervention program costs include GP and PN training time, time for 2 consultations in the GPC, costs for program updates, and user licenses divided by a conservative number of potential annual users. Costs for the development of the intervention as well as research-specific costs were excluded.

Incremental cost-effectiveness ratios and incremental cost-utility ratios will be calculated by comparing the costs and effects (probability of maintaining a healthy lifestyle and QALYs) of the usual care group with those of the intervention group. Statistical differences in nonnormally distributed costs and QALYs will be tested using bootstrapped 1-tailed *t* tests. A cost-effectiveness acceptability curve will be constructed with the bootstrapped incremental cost-effectiveness ratio to visualize the probability that the blended care intervention is cost-effective at specific willingness-to-pay thresholds. The ceiling ratio for the cost-utility of the interventions will be set at €20,000 (US $20,900.80) per QALY. This is an accepted Dutch cutoff point for the willingness to pay for each QALY gained by preventive interventions and is commonly used to evaluate this type of intervention in the Netherlands [46,50-52].

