## Results

This study was funded in July 2020. Data collection started in August 2022 and is likely to be completed by April 2025. As of December 2024, this study is still ongoing. Data analysis is estimated to start in the spring of 2025. A total of 127 participants have been recruited across 26 GPCs in the Netherlands. The first results are expected to be published in 2026.

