### Strengths and Limitations

#### Overview

This paper describes the study protocol for an RCT of the effectiveness of a blended care intervention for cancer aftercare in general practice. Conducting an RCT strengthens our interpretation of the results by controlling for confounding through randomization. In addition, the current research is very similar to the previous research evaluating the effectiveness of the online-only CAG intervention, which allows the results to be compared and the added value of blended care to be identified. The blended care format is being added to increase the reach of our intervention, specifically targeting a population that would not access an online-only intervention on their own. The blended care protocol has been developed in cocreation with survivors, GPs, and PNs to ensure the best fit with the general practice context and the needs of survivors ([name], unpublished data, 2025). However, some challenges cannot be foreseen. Conducting the RCT in a period following the global COVID-19 pandemic may place limitations on our study protocol. For example, it may be difficult to achieve our target sample size due to recruitment problems with both GPCs and survivors of cancer. In the aftermath of COVID-19, the health care sector is facing a workforce shortage, partly due to the retirement of a large proportion of the working population [55,56]. In primary care, this is leading to the closure of GPCs as owners are not being replaced by a new generation. Meanwhile, the COVID-19 pandemic has resulted in a high rate of delayed care, further increasing the demand for GPCs and leaving little room for trial participation and research activities such as patient recruitment. This resulted in a difference in the number of GPCs recruited compared to our target. We aimed to recruit 40 GPCs, but in reality, only 26 GPCs were recruited.

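### The stated sample size of 282 (376 enrolled) at 80% power does not follow from the inputs printed beside it

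*Protocol article*

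**What the plan says.** The Sample Size section of the protocol article expects a larger effect at the first follow-up ("In the current design, we expect an ES of 0.40 at 6 months follow-up") and a smaller one later ("we estimate an ES of 0.30 at 12 months"). It sizes the trial on the smaller: "Sample size calculation (ES=0.30; power=0.80; intracluster correlation=0.03, design effect 1.27) indicates that 282 participants are required", which is 141 per condition. It then allows for 25% dropout and arrives at 376 to be enrolled (188 per condition), to come from about 40 general practice centers (GPCs) with 10 participants each.

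The paragraph gives no alpha, no sidedness and no baseline/follow-up correlation. The article's only mention of sidedness is in the Economic Evaluation section and concerns costs and QALYs: "Statistical differences in nonnormally distributed costs and QALYs will be tested using bootstrapped 1-tailed" t tests.

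The Statistical Methods section plans multilevel regression on residual change scores, at 6 months and at 6 and 12 months combined. The Results section reports, as of December 2024: "A total of 127 participants have been recruited across 26 GPCs in the Netherlands". The Strengths and Limitations section adds: "We aimed to recruit 40 GPCs, but in reality, only 26 GPCs were recruited".

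**The concern.** The article prints both the inputs and the result of one calculation, so the result can be checked. At an effect size of 0.30 and 80% power, a two-sided 5% comparison of two means already needs about 350 participants with no clustering at all. That exceeds 282 before the design effect of 1.27 is applied.

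The enrolment figure of 376 and the recruitment target in GPCs both rest on 282. Readers of the results will weigh them against a published claim of 80% power at 0.30. If the printed inputs do not support that claim, a non-significant result could be given more weight against the expected effect than it deserves.

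**Working it through.** **Inputs from the Sample Size section:** effect size (ES) 0.30; power 0.80; intracluster correlation 0.03; 10 participants per GPC; dropout 25%. **Assumed, because not stated:** alpha 5%, tried two-sided and one-sided.

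**1. Steps that reproduce**
- Design effect: 1 + (10 − 1) × 0.03 = 1.27.
- Dropout: 282 / 0.75 = 376.

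The discrepancy therefore lies in 282 itself.

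**2. Size from the printed inputs**, n per arm = 2 × ((z_alpha + z_power) / ES)²
- Two-sided: 2 × ((1.960 + 0.842) / 0.30)² = 174.4, so 175 per arm (176 by t test), or 350 to 352 in total. Times 1.27: 444 to 446 analysed. Divided by 0.75: about 592 to 595 enrolled.
- One-sided: 2 × ((1.645 + 0.842) / 0.30)² = 137.4, so 138 per arm (139 by t test), or 276 to 278 in total. Times 1.27: 350 to 352 analysed. Divided by 0.75: about 467 to 470 enrolled.

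A design effect based on 7.5 completers per GPC (1 + 6.5 × 0.03 = 1.195) gives 418 two-sided or 330 one-sided. Using ES 0.40 with 1.27 gives 250 or 198. None of these is 282.

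**3. Power of 282 on the printed inputs**
- Effective n per arm: 141 / 1.27 = 111.0.
- Standardised difference: 0.30 × √(111.0 / 2) = 2.235.
- Two-sided power: Φ(2.235 − 1.960) = 0.61. One-sided: Φ(2.235 − 1.645) = 0.72.

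**4. What could lie behind 282**
- One-sided with the design effect left out: 276 to 278. This is close, but it contradicts the printed 1.27.
- Two-sided with 1.27 and a baseline/follow-up correlation r: 282 / 1.27 = 222, and 222 / 348.8 = 0.637 = 1 − r², so r is about 0.60. With r = 0.60 exactly, 348.8 × 1.27 × 0.64 = 283.5, or 284 in whole pairs.
- A gain from combining the two follow-ups. If they correlate at r, the variance of their mean is (1 + r)/2 of a single one. At 282 and ES 0.30 two-sided, power is then Φ(2.235 / √0.625 − 1.960) = 0.81 for r = 0.25, and Φ(2.235 / √0.90 − 1.960) = 0.65 for r = 0.80.

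Each route needs either an input that the paragraph does not print or the omission of one that it does.

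**5. Secondary: the enrolled number**, ES 0.30, two-sided 5%, no baseline gain, 127 participants in 26 GPCs
- No dropout: 127 / 26 = 4.88 per GPC; design effect 1 + 3.88 × 0.03 = 1.117; effective N 113.7; power Φ(0.30 × √(113.7 / 4) − 1.960) = 0.36.
- 25% dropout: 95.25 analysed, 3.66 per GPC; design effect 1.080; effective N 88.2; power Φ(1.409 − 1.960) = 0.29.
- 25% dropout with the planned 1.27: effective N 75; power Φ(1.299 − 1.960) = 0.25.
- 25% dropout, design effect 1.080 and r = 0.60: effective N 88.2 / 0.64 = 137.8; power Φ(1.761 − 1.960) = 0.42 (0.41 to 0.42 allowing for rounding and method).
- One-sided without baseline gain, over the same dropout and design-effect choices: 0.37 to 0.48.

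**The case against.** The best defence is that the formula above is not the planned analysis. The primary outcomes are residual change scores, which use the baseline, and the tests are at 6 months and at both follow-ups combined; no test at 12 months alone is listed. At 6 months the article expects ES 0.40, where 282 with a design effect of 1.27 gives Φ(0.40 × √(111.0 / 2) − 1.960) = 85% two-sided with no baseline gain.

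For the combined analysis, assume equal correlations r between all time points and ES 0.30 on the raw scale. Baseline adjustment plus averaging then gives a variance factor of (1 + r)/2 − r², which is at most 0.5625. The requirement is then at most 348.8 × 1.27 × 0.5625 = 249. In addition, a journal article may leave alpha, sidedness and correlation assumptions to the full protocol.

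Much of this stands. A reader might infer that the true power of the design is 61%, but the documents do not support that: the figure depends on sidedness, on the scale of the effect size and on the model. Nor can an undisclosed input be excluded. The defence does not rescue the paragraph, however. It presents 282 as the output of the listed inputs, and it is not. If the 0.30 is already on the residual-change scale, the baseline gain has been counted and cannot be taken again. If it is on the raw scale, the assumption that would cut the size by 36% is not printed.

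A second tempting reading is that the article wrongly claims 80% power for the sample it has. It does not. It makes no power claim for 127, dates that count within an ongoing study and discloses the shortfall in GPCs. It also plans confidence intervals and Bayes factors, which help to separate inconclusive data from evidence of no effect.

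**Conclusion.** The point holds as a mismatch between printed inputs and printed result. At an assumed 5% alpha, the stated 282 falls short of what the inputs require by about 163 analysed participants two-sided (445 − 282) or about 68 one-sided (350 − 282). Taken at face value, the inputs give 282 a power of 61% or 72%, and not 80%. These two percentages are conditional on the printed inputs and a single baseline-free comparison. An unprinted correlation near 0.60 would bring power back to about 80%.

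The low power at 127 participants (roughly 25 to 36% two-sided without baseline gain) is a consequence of under-recruitment and not an arithmetic error. It matters only because the 0.80 should not be read as the power achieved.

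**What to change.** Correct the sample-size paragraph in one of three ways:
- give the size that the listed inputs require: about 445 analysed and 595 enrolled two-sided, or about 350 and 470 one-sided, with alpha and sidedness stated;
- keep 282 and restate its power at ES 0.30 as about 61% two-sided (72% one-sided);
- keep 282 and 0.80, and name the alpha, sidedness and correlation or repeated-measures assumption that yields them, saying on which scale the effect size is defined.

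In addition, describe 0.80 as the planned target, since 127 participants in 26 GPCs had been enrolled by December 2024.

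The cost is wording only, although the stated power may become less favourable. Analysis was not due to start until spring 2025, after the December 2024 status report, so the article itself describes a point at which the correction could precede any result. No extra enrolment is asked for.
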